#### Safety assessments

There are few anticipated adverse effects of this structured lifestyle intervention. The development of the intervention ensured that it was tailored to the needs of people with schizophrenia, schizoaffective disorder and first-episode psychosis. There is a risk that anxiety about weight and its complications may be increased. If the intervention is unsuccessful this may lead to feelings of poor self-esteem. These risks probably are outweighed by the risk of widening health inequality and worsening health among people with schizophrenia if the intervention is not assessed.

The following are expected serious adverse events for the patient population:Psychiatric hospitalisationSelf-harmSuicide attemptDeath from suicide

Adverse events will be monitored at 3- and 12-month follow-ups. All serious adverse events that are also both ‘unexpected’ (that is, the type of event is not listed in the protocol as an expected occurrence); and ‘related’ (that is, it resulted from administration of any of the research procedures) will be reported by sites to the central team and the sponsor for expedited reporting to the trial oversight committees and the Research Ethics Committee.

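### Expedited reporting leaves out the four listed serious adverse events, including self-harm and suicide, even when judged to result from the research procedures

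*Protocol article*

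**What the plan says.** All of the rule is in the Safety assessments section of the protocol article.

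- **The list.** It is introduced with the words "The following are expected serious adverse events for the patient population" and names four event types: psychiatric hospitalisation, self-harm, suicide attempt and death from suicide.
- **The conditions.** The route applies to "All serious adverse events that are also both" unexpected and related. Unexpected is explained as "the type of event is not listed in the protocol as an expected occurrence". Related is explained as "it resulted from administration of any of the research procedures".
- **The route.** Events that meet both conditions "will be reported by sites to the central team and the sponsor for expedited reporting to the trial oversight committees" and to the Research Ethics Committee.
- **The risks named.** Anxiety about weight and its complications may rise. In addition, "If the intervention is unsuccessful this may lead to feelings of poor self-esteem".
- **Routine collection.** "Adverse events will be monitored at 3- and 12-month follow-ups". The Outcome measures section also counts adverse events among the secondary outcomes.

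**The concern.** The list and the causal judgement answer different questions. The list says which serious events are common in this population whatever treatment they receive. That is a sound reason not to expedite an event that nobody attributes to the study, since background frequency explains it. Once an event has been judged to result from the research procedures, background frequency is no longer the explanation, and the reason for the exemption has gone. The rule keeps the exemption all the same, because expectedness depends on event type alone.

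What is at stake is how quickly those responsible for participants' safety hear of a serious harm attributed to the study. The four exempt types include death, and three of the four concern self-harm or suicide. The only intervention risks that the section names are psychological, so it is reasonable to think that a serious harm from this programme, if one occurred, could take one of the listed forms. That last step is an inference; the article does not make it.

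**Working it through.** No sample size, error rate or event count bears on the point, so the check is one of logic.

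**Inputs**, all from Safety assessments:

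1. The two conditions are joined by 'and'.
2. Unexpected is defined only by the event type being absent from the list.
3. Related is defined by the event having resulted from a research procedure.
4. The list has four types and describes the patient population.
5. No exception is stated for a listed event that is judged related.

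**The rule as written:** expedited = serious AND related AND NOT listed.

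**Applied with serious = true and related = true:**

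| Event type | Listed? | Expedited? |
|---|---|---|
| Psychiatric hospitalisation | yes | no |
| Self-harm | yes | no |
| Suicide attempt | yes | no |
| Death from suicide | yes | no |
| Any unlisted type | no | yes |

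All 4 of the 4 listed types fall outside the route. For these types the relatedness judgement has no effect: with related = true or related = false, the result is 'not expedited'. For unlisted types it decides the outcome.

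**The alternative rule:** expedited = serious AND related. With related = true, all five rows become 'yes'. With related = false, every row stays 'no', as it does now. The only events whose handling changes are those both listed and judged related, so no unrelated event is added to the expedited workload.

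**The case against.** The strongest reply has three parts.

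*The article is a condensed source.* It gives one sentence to the expedited route and does not say how other serious adverse events are passed on. The full protocol may contain a separate route for related events of a listed type. This is a fair limit, and the sponsor could settle the point by citing such a route. It does not remove the point, because the article does more than stay silent: it states a rule, and that rule has no exception.

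*Requiring an event to be both related and unexpected is a common form of test.* That is so, and the form is not the complaint. The weakness lies in pairing it with a list based on the population, so that a judgement of causation cannot change the outcome.

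*Other oversight exists.* Under Trial supervision, the DMEC has access to unblinded outcome data while the trial runs, and adverse events are a secondary outcome. This stands, and for that reason no additional committee tables are asked for here. Such access does not give these events an expedited route.

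A reader might go further than the article supports, in three ways.

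- One might infer that a related event could go unnoticed for the 9 months between the 3- and 12-month visits (12 − 3). That interval comes from the visit schedule, not from the expectedness rule. An unlisted event found only at a visit would wait just as long, and the fix below would not shorten the wait. The STEPWISE education programme section also describes support contact about every 2 weeks and booster sessions at 4, 7 and 10 months for the intervention arm. The article does not say that facilitators report adverse events, but it gives no ground for calling such events unseen.
- One might infer that events would be lost for the 20 % assumed to drop out. In the Sample size section that figure is a conservative allowance for the primary outcome, not a forecast of missing safety data, and the article allows additional information to be taken from patients' notes.
- One might call the section self-contradictory because it names poor self-esteem and yet exempts self-harm. It does not itself connect the two, so this is not an internal contradiction.

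**Conclusion.** The point holds as a weakness in a stated reporting rule, and the rule should be changed. Its extent is exact: four of four listed event types are outside expedited reporting even when judged to result from the research procedures. How many events this would affect cannot be derived from the article; events that are both serious and judged related should be few.

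The conclusion assumes that the sentence is meant literally and that no other document overrides it. It does not say that these events go unrecorded, that the committees would never learn of them, or that the intervention causes self-harm. Sample size and analysis are unaffected.

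**What to change.** Amend the sentence in Safety assessments so that every serious adverse event judged to have resulted from the research procedures is expedited to the sponsor, the oversight committees and the Research Ethics Committee, whether or not its type is listed. State that the list of expected events serves only to exempt events judged unrelated. If the full protocol already provides an equivalent route for related events of a listed type, a reference to it would be enough.

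The cost is one sentence, revised instructions to the 10 participating trusts, and a few more expedited reports. According to Trial status, recruitment has closed and the trial is in follow-up, so the instructions would reach sites part-way through and would apply to the remaining follow-up.

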### Sample size

The sample size calculation is based on data obtained from two sources, both of which evaluated behavioural interventions for weight loss in people prescribed antipsychotic medication for schizophrenia. Das et al. undertook a systematic review of randomised and nonrandomised controlled trials which reported between-group differences of 1.5 to 6 kg with standard deviations of around 5 kg [34]. The second source was data on overweight and obese UK patients with severe mental illness in which 51 people with schizophrenia were followed up for at least 1 year; among these, the weight change was 7.7 kg with a standard deviation of 6.5 kg [35]. We propose to detect a difference of 4.5 kg, which is both clinically meaningful (being on average around a 5 % reduction in body weight) [36] and appears compatible based on previous work. Assuming a conservative estimate of the standard deviation (SD) of 10 kg, 95 % study power, and two-sided significance level of 5 %, 130 participants per arm (260 in total) are required in order to detect a minimum clinically important difference of 4.5 kg.

Since the intervention is delivered in groups, the outcomes of the participants within the same group may be correlated. Assuming on average of seven participants per group, and an intraclass correlation of 5 % in the intervention arm, the sample size will be inflated by a design effect of 1.3 in the intervention arm in order to allow for this, which yields revised sample sizes of 169 and 130 in the intervention and control arms, respectively (299 in total). To maintain a 1:1 allocation, 158 participants per arm are required to reproduce this power. We further anticipate a conservative dropout rate of around 20 % (higher than that observed in similar studies [37], giving a final total of 198 participants per arm. With 10 centres, this requires 40–50 participants per centre (rounded upwards), 20–25 of whom will receive the intervention in three to four groups.

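### The 158 per arm for 1:1 allocation does not follow from the inputs printed beside it (about 150, or 153 with group-based degrees of freedom); the discrepancy is conservative

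*Protocol article*

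**What the plan says.** The Sample size section of the protocol article prints a complete chain of figures.

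- Target difference: "We propose to detect a difference of 4.5 kg".
- Variability: "Assuming a conservative estimate of the standard deviation (SD) of 10 kg".
- Error rates: "95 % study power" and a "two-sided significance level of 5" %.
- Size before clustering: "130 participants per arm (260 in total) are required".
- Clustering: seven participants per group on average and an intraclass correlation of 5%, giving a design effect of 1.3 that is applied to the intervention arm alone, "which yields revised sample sizes of 169 and 130 in the intervention and control arms, respectively (299 in total").
- Return to equal arms: "To maintain a 1:1 allocation, 158 participants per arm are required to reproduce this power".
- Dropout of about 20%, "giving a final total of 198 participants per arm".

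The Abstract carries the resulting total of 396. No formula or method is given for the step from 169/130 to 158/158.

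**The concern.** Each figure is presented as the consequence of the one before it. When the chain is followed by hand, every step reproduces except the return to equal arms. That step fixes the pre-dropout size, so 198 per arm and 396 in total both rest on it.

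What is at stake is modest. The evaluable number that delivers 95% power is the natural yardstick for 12-month retention. With 198 randomised per arm, a requirement of 150 is met at 150/198 = 76% retention, 153 at 77%, and 158 at 80%. A reader cannot tell from the text which of these is meant.

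**Working it through.** **Inputs**, all from the Sample size section: difference δ = 4.5 kg; SD = 10 kg (variance 100); two-sided α = 5%; power 95%; group size m = 7; ICC = 0.05 in the intervention arm; dropout 20%.

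**Step 1, size before clustering.** n = 2 × 100 × (1.960 + 1.645)² / 4.5² = 128.3, so 129 by the normal approximation. The t-test needs 130 (power 95.1%). The stated 130 reproduces.

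**Step 2, design effect.** 1 + (7 − 1) × 0.05 = 1.3, and 130 × 1.3 = 169. The stated 169/130 (299) reproduces.

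**Step 3, equal arms.** With the design effect in one arm only, the variance of the difference is 100 × (1.3 + 1)/n. Setting it equal to the unclustered 100 × 2/130 gives

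n = 130 × (1.3 + 1)/2 = 149.5, so 150 per arm.

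The stated figure is 158. To obtain 158 from this formula the design effect would have to be 2 × 158/130 − 1 = 1.43, that is an ICC of about 0.43/6 = 0.072 at seven per group.

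**Step 4, dropout.** 158/0.8 = 197.5, so 198, which reproduces. From 150 it would be 187.5, so 188 per arm and 376 in total: 20 fewer than 396, or 5%.

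**Alternative methods for step 3.** Let a = V₁/n₁ and b = V₂/n₂, with V₁ and V₂ the effective variances in the intervention and control arms. Power comes from δ/√(a + b), using the normal distribution or the noncentral t. The Satterthwaite degrees of freedom are (a + b)² / [a²/(k − 1) + b²/(n₂ − 1)], where k = n₁/7 is the number of groups.

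- Total SD 10: V₁ = 130, V₂ = 100.
- Residual SD 10 with group variance added: V₁ = (100/0.95) × 1.3 = 136.8, V₂ = 100.

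| Method | Power, 169/130 | Power, 150/150 | Power, 158/158 | Equal n for 95% |
|---|---|---|---|---|
| Normal, total SD 10 | 95.2% | 95.3% | 96.2% | 148 |
| t, N − 2 df, total SD 10 | 95.1% | 95.2% | 96.1% | 149 |
| Satterthwaite, total SD 10 | 94.8% | 94.7% | 95.7% | 153 |
| Satterthwaite, residual SD 10 | 94.2% | 94.1% | 95.1% | 158 |

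The last row is the variant that returns 158 (157 gives just under 95%). In no row do 169/130 and 158/158 have the same power; the gap is about one percentage point throughout.

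**The case against.** The strongest defence is that 150 is the answer to one method, not the only one the inputs allow. The Data analysis section specifies GEE with robust standard errors, and there would be only about 150/7 ≈ 21 groups in the intervention arm, so degrees of freedom based on groups are a reasonable choice. A recognised partially nested calculation does return 158, and the quoted sentence, which speaks of reproducing power, is compatible with a calculation of that kind. This stands to the extent that 158 cannot be called underivable, and that replacing it with a flat 150 would be unsafe: 150 gives 94.7% or 94.1% under the two Satterthwaite rows.

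It does not rescue the text. The residual-SD reading makes the intervention-arm variance 1.37 times that of the control arm, where the section says 1.3. It also requires the method to change silently between adjacent sentences, because 169 is plain 130 × 1.3. And on that reading 169/130 falls short of 95%.

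It can also be said that an article condenses a fuller protocol, so the formula may be given there. That excuses a missing formula. It does not excuse a printed figure that disagrees with the figures printed next to it.

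A reader might infer that the sample size and the 95% power conflict, or that the trial is underpowered. The document does not support either: 158 per arm meets 95% under every method in the table. Nor does the error spread to everything downstream. The lower figure of 40 per centre is unaffected, since 376/10 = 37.6 and 396/10 = 39.6 both round up to 40, and none of the criteria in the Internal pilot section uses 158.

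**Conclusion.** The sentence is wrong as written. Under the stated design effect, equal allocation needs about 150 evaluable per arm (153 with group-based degrees of freedom), and 158 per arm exceeds the power of 169/130 by about one percentage point instead of reproducing it. The discrepancy is on the safe side: about 96% power in place of 95%, and about 20 participants in total after dropout, or 12 if 153 is taken as the requirement (153/0.8 = 191.25, so 192 per arm and 384 in total).

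This rests on reading the SD of 10 kg as the total SD, as the 130 and 169 figures imply, with seven per group, an ICC of 5% and clustering in one arm only. The residual-SD explanation of 158 is an assumption about how the figure arose; the document neither states nor excludes it.

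The Trial status section reports 414 recruited. If these split equally, 207 per arm with 20% loss leaves 165.6 evaluable, above all the requirements computed here. Severity is minor.

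**What to change.** Make the chain consistent, in one of two ways.

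1. If the design effect of 1.3 governs: state that about 150 evaluable participants per arm (153 allowing for the small number of groups) give 95% power, and that the retained target of 158 evaluable, 198 randomised, per arm gives about 96%.
2. If 158 came from a partially nested calculation: state its variance definition and degrees of freedom, and correct the 169/130 figures so that they follow from the same method.

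The trial team should know which applies. The cost is a sentence or two in the Sample size section, and in any analysis plan that repeats the figures. The recruitment target and the conduct of the trial do not change.

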### Internal pilot

The trial includes an internal pilot which will assess whether it is feasible to recruit and retain sufficient participants. By 11 September 2015, the middle of the project (month 24):Ten centres should have been initiated and should have recruited their first participantTwo hundred and fifty participants should have been recruitedSix centres should have completed their first STEPWISE courseNinety-six participants should have been followed up to their 3-month outcome assessment

The trial will be considered infeasible and will be stopped if one or more of the following conditions apply:Fewer than six centres have recruited their first participantFewer than 125 participants have been consentedFewer than three centres have completed their first 4-week STEPWISE courseFewer than 75 % of those followed up to their 3-month outcome assessment have contributed valid weight (primary outcome at 12 months) data at this time point

### Data analysis

Data will be analysed and reported according to the guidelines of the revised CONSORT statement for randomised controlled trials [25].

The analysis will be performed on an intention-to-treat basis and all statistical tests will be two-tailed at 5 % significance level. Demographics and baseline characteristics will be summarised and assessed for comparability between the intervention and control arms [38, 39].

The primary outcome will be assessed by fitting a marginal generalised estimating equation model (GEE) adjusted for baseline weight, using robust standard errors and an exchangeable correlation structure. This model incorporates an adjustment for potential clustering or correlation among the outcomes of participants treated in the same group. A 95 % confidence interval for the difference in weight between the lifestyle intervention and control arms will be reported with its associated *P* value. A sensitivity analysis will be performed in the same manner, which will include baseline covariates and any observed imbalances. In case of missing data, the missing data mechanism will be explored and multiple imputation approach applied to assess the robustness of the findings.

Of key interest is whether the intervention conveys the same effect among recently diagnosed patients (i.e. patients experiencing first-episode psychosis) as it does among those established on antipsychotic medication for a greater period of time. We will investigate this in the analysis by fitting an interaction term between treatment group and the time since starting antipsychotic medicine (including a nonlinear term if appropriate). The treatment effect will be presented graphically for different subgroups of the time elapsed since commencing medication.

Other continuous outcomes will be analysed and reported in the same manner as the primary outcome. Analysis of binary outcomes will be undertaken using a marginal generalised logistic linear regression model within the GEE framework and difference between treatment groups will be reported as odds ratios with associated 95 % confidence intervals and *P* values.

### Economic evaluation

The economic evaluation will be from a health and social care and societal perspective. The number of intervention sessions received will be centrally recorded. The cost of the intervention will be based on staff time plus overheads (capital and administrative) and an element for training and supervision. Other service use will be recorded at baseline and at 3- and 12-month follow-ups using the interviewer-administered Client Service Receipt Inventory, and will include:primary caresecondary care, including inpatient costs (specialist mental health and physical health services)social carepsychotropic and other medication, andinformal care from families or friends (expressed in terms of hours per week spent on specific tasks because of the participant’s health problems)

Service costs will be calculated by combining the above data with appropriate unit cost information [40, 41]. Informal care time will be valued using average wage rates with sensitivity analyses using minimum wage rates and the value of a homecare worker. Lost work time will also be recorded for those in employment and valued using average wage rates. Total health and social care costs and societal (i.e. including informal care and lost employment) costs will be reported and compared between the two groups for the 1-year follow-up. A regression model will be used with baseline costs controlled for and bootstrapped 95 % confidence intervals generated given the expected skewed cost distribution.

Cost-effectiveness will be assessed by combining the cost data (from both perspectives) with the primary outcome measure and QALYs. The latter will be generated from the EuroQol five dimensions, five levels questionnaire (EQ-5D-5L) using UK tariffs and area under the curve methods. If the intervention results in lower (higher) costs and better (worse) outcomes then it will be dominant (dominated). In the event of higher costs and better outcomes (or lower costs and worse outcomes), incremental cost-effectiveness ratios (ICERs) will be constructed to show the cost per extra unit of weight loss or extra QALY gained. Uncertainty around the ICERs will be addressed by constructing cost-effectiveness planes using 1000 bootstrapped cost-outcome pairs and cost-effectiveness acceptability curves (CEACs). The latter will indicate the probability that the intervention is more cost-effective than TAU for different threshold values placed on a unit reduction in weight or one more QALY gained. The NICE uses a threshold of £20,000–30,000 for a QALY gain and so the CEACs will include this value in the range of values. There are no recognised threshold values of a unit reduction in weight and so values will be reported at which the intervention or TAU has a 50 %, 70 %, 80 % and 90 % likelihood of being the most cost-effective option.

Sensitivity analyses will be conducted by varying the costs of the intervention, informal care and lost employment. QALYs based on the SF6D (derived from the RAND Short Form 36-item Health Survey; SF-36) will also be used in sensitivity analyses given that this arguably has better distributional properties than EQ-5D-5L-based QALYs in this patient population [42]. The EQ-5D-5L has a clear ceiling effect in people with schizophrenia while the SF6D is normally distributed.

